## Discussion

National Governments in sub-Saharan Africa have demonstrated strong leadership in the response to the recent food and financial crises by scaling-up school feeding programmes. “Home-grown” school feeding programmes have the potential to link the increased demand for school feeding goods and services to community-based stakeholders, including small-holder farmers and women’s groups. However, there is a dearth of evidence on the costs and benefits of school feeding programmes linked to small-holder agriculture and community development. This evaluation will be the first to examine the impact of linking school food service provision on small-holder farmer income, as well as the link between community level engagement and programme performance, alongside assessing the more traditional benefits to school children.

The impact evaluation follows a theory-based approach and is underpinned by the development of the programme theory for the intervention. It includes a process evaluation component that will enable policymakers to not only understand if the intervention works or not, but also why and how it is working. By using a mixed-method approach, the evaluation will explore both hard outcomes (for example, enrolment, income, welfare) but also perceptions on softer elements of programme performance (for example, community ownership and accountability).

This study will also be the first evaluation designed around the scale-up of a national school feeding programme in sub-Saharan Africa. It is a prime opportunity to provide policy relevant evidence. To ensure that this was the case, policy makers across Education, Health, Agriculture and Local Government Ministries were engaged from the early design stages through to survey design and implementation. In particular, this study is anchored in the framework provided by the Ministry of Education’s recently developed national school feeding policy. In Mali, the national policy on decentralisation also meant that policy makers at regional and commune level be engaged in design process. A number of meetings were held to sensitise stakeholders at the different levels, also including them in the randomisation process.

Conducting this type of research in the Malian context also raises a number of practical issues, including logistics, security and local political constraints. A set of contingency plans were developed to tackle foreseen challenges; however, the major upheaval currently taking place in the country clearly poses a major challenge to the intervention itself. The scale-up areas, however, remain under Government control, and recent news provides encouraging signs that the work will continue. Despite these challenges, the study is underway, and the baseline survey will provide some important new data on the links between education, health and small-holder agriculture in food insecure areas of Mali.

## Trial status

As of April 2012, the baseline survey for this study is underway though completion is pending, depending on the current political unrest in the country.

## Appendix 1: Power calculations

The designed adopted by this study consists of (a) a multi-site cluster randomized trial to detect the impact of the regular school feeding and HGSF+ intervention against a control group without school feeding intervention, and of (b) a cluster randomized trial to detect the impact of the HGSF+ intervention against the regular school feeding intervention.

### Comparing school feeding to no-school feeding (multi-site cluster randomized trial)

In the multi-site cluster randomized trial the sites are blocks and clusters are randomly assigned to treatment and control within each site. In each commune (site), two schools (clusters) are selected and randomly assigned to the treatment and the control groups. This is equivalent to conducting a randomization of schools stratifying by commune.

There are a total of 58 communes selected for the intervention and two schools are chosen by local education authorities in each commune. In each school/village, 25 households will be interviewed. Only families with children in the age range from 5 to 15 will be selected, which implies that some 55 children in each community and a total of more than 6,500 children will take part to the interviews. The average number of children aged 5 to 15 in rural Mali was 2.58 in 2006 based on the data collected by the DHS. Care will also be taken to obtain a sizable sample of farmers and potential providers of staples for school feeding in each village.

We calculate power and minimum detectable effect size for the following outcomes:

•enrolment rates

•test scores

•farm income

### Enrolment

Public education in Mali is compulsory for nine years from age 7 to age 15 and split in a six-year primary cycle and a three-year lower secondary cycle. Enrolment rates in rural areas are very low and lower for girls compared to boys. Table 6 below reports the attendance rates for the age groups 7 to 12 and 13 to 15 in rural Mali calculated from the DHS survey of 2006 (Table 6).

**Table 6 T6:** Attendance rates for the 7 to 12 and 13 to 15 age groups in rural Mali (calculated from DHS, 2006)

	**Primary (age group 7 to 12)**	**Lower secondary (age group 13 to 15)**	**Age group 7 to 15**
All	35.6	33.8	35.1
Male	39.1	39.9	39.3
Female	32.1	27.4	30.8

Ahmed [34] found a 14% difference in enrolment rates between project and control groups in Bangladesh. Researchers for FAO/WHO [21] found an effect of 6% in Burkina Faso, Jacoby [35] found a difference of 3% in Peru, while Buttenheim *et al*. [36] found no effect in Laos, mostly due to lack of intervention implementation. We adopt an increase in attendance rate by five percentage points as a minimum expected impact of the programme. Simulations of power for the percent difference in enrolment in the project group versus the control group show that a 5% difference will be detected with 80% probability, while differences of 10% and 15% will be detected with certainty. At 80% power, the minimum detectable difference is 5%.

### Test scores

Few studies have investigated the impact of school feeding on learning outcomes. Drèze *et al*. [32] reviewed the experimental evidence on the impact of school feeding on standardised test scores and found an average standardised effect size of 0.31 for math achievement tests, while no effect was found on reading tests. We adopt a 0.3 difference as the expected effect of the intervention on math test scores. Based on the Scrochet report, the recommended intra-cluster correlation coefficient for math and reading tests is 0.15. We also assume that only about half of the children interviewed will be able to take the test and we set the number of children tested per village at 25. Simulations of power as a function of minimum standardised detectable effect show that a standardised difference of 0.1 would be detected in 24% of cases, a difference of 0.2 would be detected in 68% of cases and a difference of 0.3 would be detected in 95% of cases. With power set at 80%, the minimum detectable difference is 0.23.

### Income

No previous studies have investigated the impact of home-grown school feeding on farmers’ incomes and indeed this type of programme is entirely new. In addition, it is difficult to find programmes with effects similar to those of school feeding programmes. The Purchase for Progress programme by the World Food Programme, which similarly to the Malian school feeding programme purchases food for local producers, has modelled an increase in income by $50 dollars as a reasonable target for small African farmers. With a per capita GDP of $700 this corresponds to 7.5% of the average Malian income, though the income of small farmers is likely to be less than half the national average income. In addition, farm income is about 50% of total household income and the impact of a $50 increase on farm income is therefore much larger. We adopt 15% and 30% as minimum detectable effects of the programme on agricultural incomes of small farmers.

We adopt a conservative estimate of 10 farmers surveyed in each village, and based on data on agricultural incomes of Ghanaian farmers, we estimated the intra-class correlation coefficient (ϱ = 0.25) and the variance explained by site variability (B = 0.40). Note that given the high value of the standard deviation of income, similar in size to average income, the standardised difference and the percentage difference are almost equivalent. The probability of detecting an increase by 15% in agricultural income is 35% and the probability of detecting an impact of 30% is 88%. A power of 80% will be able to detect an income increase by 26%.

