### Main hypotheses and outcome indicators

We summarise here the expected impact of the intervention on education, nutrition and social protection discussed in Section Programme theory of the intervention.

•The intervention will have an impact on a small number of farmers in the intervention villages. Other persons in the village may benefit either directly or indirectly via an increase in income.

•The intervention will have a positive impact on enrolment, attendance and drop-out rates.

•The intervention will have an impact on cognitive abilities and class behaviour, including attention.

•The impact on learning (test scores) will be moderate as school quality is unlikely to change in the short term.

•The intervention will have a limited impact on physical growth of children because of the increase in PAL, substitution effects and the age range (6 to 17 years) of the targeted population. An impact on siblings of school-going children is possible if substitution effects are strong.

•The intervention will have a moderate impact on the diet because food purchases by communities and mayors do not follow nutritional guidelines and nutrition education is absent.

•The intervention will have little or no impact on micronutrient status as the food provision is not fortified and only moderate effects on diet diversity are expected.

•The overall impact of the programme will increase through the introduction of social accountability mechanisms and the strengthening of the monitoring and communication system.

Table 2 includes a list of the main outcome indicators of the study. Section Methods of analysis will describe how data will be collected using different survey instruments. All outcomes, including school attendance and test scores, will be obtained at the household level.

**Table 2 T2:** Main outcome indicators of the intervention

** Indicator**	** Metric**
Income	Farm profits
Distributional effects	Small farmers participating in the programme
Schooling	Enrolment, attendance, and completion
Attention	Digit span or other test
Learning achievements	Scores on language and math tests
Physical growth	Anthropometric measures of height and weight
Diet diversity	Household consumption
Social accountability	Parental monitoring and motivation

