In practice, the sampling of households was not conducted via a previous census as this was considered too costly in terms of time and resources. We opted for interviewing village chiefs and building a list of enlarged households in the villages covered by the sample school. The listing also included an approximation of the size of the enlarged households. In addition, a number of farmer households was oversampled in each village. Chiefs (and members of the CGSs) were asked to list which farmers they would contact if they were to purchase food within the village for the provision of school meals. This latter information was used to single out the surplus farmers in the area (up to 10 in the project villages and up to 5 in the control villages that will be interviewed).

Enlarged households were randomly selected (with inclusion probability proportional to size) from the list provided by the village chiefs, and listings of the restricted households within each selected enlarged households will then be developed through interviews with household heads. A restricted household with children aged 5 to 15 was then randomly selected within each selected enlarged non-farmer household, and we estimate that each household will have at least two children in this age group. A similar selection procedure was used for farmer households when these exceed the numbers of 10 and 5 in the project and control villages, respectively. In farmer households though, no age criteria were used and the household was identified around the main agricultural holding unit of the enlarged household. This consists of the family members involved in the main production unit (land and livestock) in the enlarged household.

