### Conclusions

The power analysis suggests that the study will be able to detect an increase in enrolment by 5%, a 0.2 difference in test scores and an increase in farmers’ incomes by 25% between the school feeding interventions and the control group. The study will be able to detect changes in enrolment by 6%, differences in tests scores by 0.3 and changes in income by 40% between the regular school feeding and the HGSF+ components of the intervention see (Table 7).

**Table 7 T7:** Summary table of values used in the power calculations

	**Enrolment**	**Test scores**	**Agricultural income**
Alpha	0.05	0.05	0.05
N (observations)	55	25	10
J (schools)	2	2	2
K (clusters)	58	58	58
Intra Cluster Correlation	-	0.15	0.25
Between sites variability	-	0.20	0.40

While the sample size is well suited to the analysis of programme impact on attendance rates and test scores, it is clearly insufficient for the analysis of income effects of the HGSF+ intervention. However, we hope to overcome this problem in two ways: by increasing statistical power through restricted randomisation and by focussing on intermediate outcomes rather than on household income, a variable that has large variance and high within cluster correlation. First, in order to increase statistical power we will adopt ‘restricted randomisation’ [25]. We will use the baseline data collected at the village and school levels to remove the randomisation outcomes that would result in an unbalanced comparison of project and control communes. The randomisation of the HGSF+ component of the project within the 58 communes will be performed only within the restricted sample of balanced randomisation outcomes. Second, we will analyse intermediate indicators of household income such as input use (labour and other farm inputs, such as land, seeds and fertiliser) and farm capital use like animal traction, tools and simple machinery.

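### The 15% and 30% income effects rest on a $50 gain divided by a per-person income, while the analysed outcome is farm profit of a household, so the link from these effects to the $50 benchmark is not supported

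*Protocol article*

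**What the plan says.** The Income section of Appendix 1 borrows a $50 target, modelled for small African farmers by a food-purchase programme, and scales it: "With a per capita GDP of $700 this corresponds to 7.5% of the average Malian income". It adds that small farmers probably earn less than half the national average and that farm income is about half of household income, then adopts 15% and 30%.

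To move from percentages to standardised effects it treats the two as practically interchangeable: "given the high value of the standard deviation of income, similar in size to average income, the standardised difference and the percentage difference are almost" the same. Among its other inputs are "We adopt a conservative estimate of 10 farmers surveyed in each village" and, from Ghanaian farmers' agricultural incomes, "we estimated the intra-class correlation coefficient (ϱ = 0.25) and the variance explained by site variability (B = 0.40"). The printed results against control are 35% power for a 15% increase, 88% for a 30% increase, and a 26% increase detectable at 80% power.

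The unit of analysis is set elsewhere. Table 2 gives the metric as "Income Farm profits", and the text above it says that all outcomes are obtained at household level. The sampling section counts farmers as farmer households and explains that "the household was identified around the main agricultural holding unit of the enlarged household". The Conclusions of Appendix 1 also refer to the variable as household income.

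**The concern.** A percentage increase can be read as a standardised difference only if the percentage is taken over the mean of the unit whose SD is used. Here the SD is said to be about equal to mean income, so the divisor has to be mean farm income of the analysed unit, which is a farm household. The divisor actually used starts from per-capita GDP. The passage also mixes units within itself, because it applies a share of household income to a per-person figure.

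The $50 is the only external benchmark offered for the effect sizes of a primary outcome. If one $50 gain is spread over a household's farm income, it is a smaller fraction than 15% to 30%, and the power quoted for those fractions says little about the benchmark. A reader who takes 88% as the chance of seeing a $50 gain would treat a null income result as evidence against that gain.

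**Working it through.** **Inputs.** From Appendix 1: 58 communes with two schools each ("In each commune (site), two schools (clusters) are selected and randomly assigned to the treatment and the control groups"); alpha 0.05, taken as two-sided; n = 10 farmers per village in both arms, kept as printed to isolate this point; ICC 0.25; site share B = 0.40; $50 gain; $700 per-capita GDP; the two halvings. From the note to Table 3: 1.5 children per farmer household. Not in the document: household size, the unit of the $50, and the unit of the SD.

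**Step 1: the plan's power.** For a multi-site cluster design, the variance of the standardised contrast is [s² + (4/J)(ρ(1−B) + (1−ρ)/n)]/K with J = 2 and K = 58, tested by F with 1 and 57 df.
- Bracket without s²: 2 × (0.25 × 0.60 + 0.75/10) = 2 × 0.225 = 0.45.
- s² = 0: SE = √(0.45/58) = 0.088; power 38.8% and 91.7%; detectable effect 0.251.
- s² = 0.05: SE = √(0.50/58) = 0.093; power 35.5% and 88.8%; detectable effect 0.265.

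A between-site effect variance of 0.05, which the document does not state, reproduces the printed 35%, 88% and 26% closely. The power model is therefore not in dispute.

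**Step 2: where 15% and 30% appear to come from.**
- 50/700 = 7.1% (printed as 7.5%).
- 50/(700 × 0.5) = 50/350 = 14.3%.
- 50/(350 × 0.5) = 50/175 = 28.6%.

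The text says only that 15% and 30% are adopted, so this is a reconstruction, but it follows the order of the passage. Every divisor is per person. None is multiplied by household size.

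**Step 3: the same $50 on the household scale.** Assume that the $50 accrues once per farm household, that the SD is for farm units and about equal to their mean, and that a holding has m persons at $175 farm income each. Then the effect is 50/(175m) = 28.6%/m, and the 26% detectable increase is worth 0.26 × $175 × m. Power is shown for s² = 0.05, then s² = 0.

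| m | mean farm income | $50 as share | power | 26% in dollars |
|---|---|---|---|---|
| 1 | $175 | 28.6% | 86% to 89% | $46 |
| 2.5 | $437.50 | 11.4% | 23% to 25% | $114 |
| 3.5 | $612.50 | 8.2% | 14% to 15% | $159 |
| 5 | $875 | 5.7% | 9% to 10% | $228 |
| 8 | $1,400 | 3.6% | about 7% | $364 |

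m = 2.5 is one adult plus the plan's 1.5 children. m = 3.5 adds a second adult. Values up to 8 are assumed.

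**Step 4: sensitivity to the unit of the $50.** If the $50 is per household member, numerator and denominator both scale with m, and the share stays at 28.6% for any household size.

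**The case against.** The strongest reply is that the printed figures are not wrong. The appendix attaches 35% to a 15% increase and 88% to a 30% increase, and both reproduce. Its Conclusions state detectable changes as percentages, with no dollar figure. This stands: a reader might infer that the true income power is 7% to 15% instead of 35% to 88%, and the documents do not support that. Those lower figures depend on an assumed household size and on assumed units for the $50 and the Ghanaian SD.

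The $175 is also approximate. The text says less than half the average, so the per-person base could be lower and the shares correspondingly higher.

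A further reply is that the plan is already cautious about income. The section on other general equilibrium effects warns that only a few farmers per village may benefit and that comparisons with control may not reach significance, and it adds simulation analyses. Intermediate income indicators are planned, and the Conclusions call the sample insufficient for income in HGSF+ versus regular feeding. This stands in part. It makes misreading of a null result less likely, but none of it tells the reader how the detectable increase against control compares with $50. The explicit admission of insufficient sample in the Conclusions concerns only the HGSF+ contrast.

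Finally, the sample was also shaped by the communes the ministry selected and by resources, so no design choice turns on the $50. That is fair, and it limits the point to justification and interpretation.

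**Conclusion.** The point holds as a mismatch of units in the justification of the effect sizes. The $50 benchmark is expressed over a per-person base and then used for an outcome measured per farm household, and the step from percentage to standardised difference needs the mean of the analysed unit. The printed power and the 26% detectable increase remain correct for the percentages they describe.

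The size is conditional. With one $50 gain per holding and a farm-unit SD, power close to 88% for that gain would require about one person per holding, which does not fit the plan's own 1.5 children per farmer household. One adult with those children already brings power down to about a quarter, and the table above gives the fall for larger assumed holdings. With a $50 gain per household member, the plan's 30% is about right. The text speaks of a target for farmers, so one gain per farmer is the natural reading, but it is not stated.

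The slip from 7.1% to 7.5% is an arithmetic error on which nothing further depends.

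**What to change.** In the Income section of Appendix 1:
- Correct 7.5% to 7.1%.
- State the unit of the $50, of the income denominator, and of the SD and ICC.
- Re-express $50 as a share of mean farm profit per holding, using the baseline farm-income module, and restate power for that share. The conditional 7% to 15% should not be printed as a result of the plan's own inputs.
- Give the 26% detectable increase in dollars per holding.

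In the Conclusions of Appendix 1, add that the income contrast with control may detect only gains well above the $50 benchmark, so a non-significant result does not rule out a gain of that size.

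The cost is some wording and one recalculation from data already planned for collection. No extra sample is needed. The downside is that the stated income power will probably look less favourable.

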Power calculations (see Appendix 1 for more details) and resource availability suggested the adoption of a sample of 25 households from the village areas of the 58 schools receiving the intervention and of 20 households in the village areas of the 58 control schools. Farmers will be oversampled in both areas in the following way: 10 out of the 25 households in the 58 intervention villages will be farmer households and 5 out of the 20 households in the 58 control villages will be farmer households. This distribution of the sample between farmers and non-farmer households and between project control groups allows the construction of comparable samples (see Table 3).

**Table 3 T3:** Summary of sample sizes

	**Communes**	**Schools**	**Households**	**Farmers**	**Children**^**1**^
Control	58	58	870	290	2,700
HGSF	29	29	435	290	1,500
HGSF+	29	29	435	290	1,500
TOTAL	58	116	1,740	870	5,700

Note: 1) the number of children in an estimate based on an average of 2 children per family in families with children and 1.5 children per family in farmer households.

Households were randomly selected in the catchment areas of the selected schools for the survey interviews.^6^ The definition of ‘household’ in Mali is not straightforward as many families share the same living compound and polygamous families are common. A recent study [27] found that adding descriptions to a “restricted” definition of household (a group of people who normally live in your household – adopted by the DHS) increases the number of adult male members reported during the interview. This, however, does have a very limited impact on household characteristics, such as per capita food consumption, assets and agricultural production. We recommend the use of the restricted definition adopted by the Rapid Household Survey 2006, which reflects the LSMS experience in collecting data in developing countries. According to this definition, a (restricted) household is a group of people who normally live and eat together. Members spending less than three months with the household within a year should be excluded. Families living in the same compound should be considered as different (restricted) households, though the consumption section of the questionnaire was carefully designed in order to take into account the common use of food resources. Polygamous households were treated as distinct households if wives live and cook in separate houses.

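### School feeding versus control: the power calculation assumes 10 farmers and 55 children in every village, but control villages are planned with at most 5 farmers and 20 households, so the stated power is modestly overstated

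*Protocol article*

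**What the plan says.** **Power inputs.** Appendix 1 (multi-site comparison) says "In each school/village, 25 households will be interviewed" and expects "some 55 children in each community and a total of more than 6,500 children". Its Income section says "We adopt a conservative estimate of 10 farmers surveyed in each village". Table 7 repeats 55 children for enrolment and 10 farmers for income, across 58 communes with two schools each.

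**Sampling plan.** Random assignment and manipulation of treatments sets 25 households, 10 of them farmers, in each intervention village. For control, "5 out of the 20 households in the 58 control villages will be farmer households". The farmer numbers are ceilings: "up to 10 in the project villages and up to 5 in the control villages". Table 3 agrees with this plan: 290 farmers in control and 290 in each of the two feeding arms.

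**Child counts.** Table 3 lists 2,700, 1,500 and 1,500 children, 5,700 in total. Its note says the counts rest on "an average of 2 children per family in families with children and 1.5 children per family in farmer households".

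**The concern.** Two sets of sample sizes are printed for the same comparison, and both cannot be right. The control arm has at most half the farmers that the income calculation uses, and fewer households than the enrolment calculation uses. Farm income and school participation are both primary outcomes in the abstract. Enrolment has no reserve: 80% power is claimed at exactly 5 points, which the protocol calls its minimum expected impact. Any shortfall in sample therefore takes the design below its own target.

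**Working it through.** **Inputs for income** (Appendix 1, Income; Table 7): 58 communes, intra-class correlation ρ = 0.25, between-site share B = 0.40, alpha 0.05. Sidedness is not stated; I assume two-sided. The protocol treats percentage and standardised differences as nearly equal.

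**Formula.** For one treated and one control village per commune, SE² = V/58 with

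V = s² + 2ρ(1−B) + (1−ρ)(1/n₁ + 1/n₀)

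where s² is the variance of the effect across communes. Power comes from a noncentral t with 57 degrees of freedom.

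**Step 1: the plan's own figures (10/10 farmers).** With s² = 0, V = 0.30 + 0.75 × 0.20 = 0.45 and SE = 0.088. This gives 39% power at a 15% increase, 92% at 30%, and a minimum detectable effect (MDE) of 25%. The protocol prints 35%, 88% and 26%. Adding s² = 0.05–0.06, which the protocol does not state, approximately recovers the printed values.

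**Step 2: the planned farmers (10/5).** With s² = 0, V = 0.30 + 0.75 × 0.30 = 0.525 and SE = 0.095.

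| Farmers | s² | V | Power at 15% | at 25% | at 26% | at 30% | MDE |
|---|---|---|---|---|---|---|---|
| 10/10 | 0 | 0.450 | 38.8% | 79.7% | 82.7% | 91.7% | 25.1% |
| 10/5 | 0 | 0.525 | 34.1% | 73.3% | 76.6% | 87.3% | 27.1% |
| 10/10 | 0.05 | 0.500 | 35.5% | 75.4% | 78.6% | 88.8% | 26.5% |
| 10/5 | 0.05 | 0.575 | 31.6% | 69.4% | 72.8% | 84.2% | 28.4% |
| 10/10 | 0.06 | 0.510 | 34.9% | 74.6% | 77.8% | 88.2% | 26.7% |
| 10/5 | 0.06 | 0.585 | 31.2% | 68.7% | 72.1% | 83.6% | 28.6% |

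In each model, halving the control farmers costs about 2 points of MDE. Because 10 and 5 are ceilings, these are best cases.

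**Step 3: children.** Table 3's household column holds the non-farmer households, since 870 + 290 = 1,160 = 58 × 20 and 435 + 290 = 725 = 29 × 25.
- By the note: control 870 × 2 + 290 × 1.5 = 2,175 (37.5 per village); each feeding arm 435 × 2 + 290 × 1.5 = 1,305 (45 per village); total 4,785.
- By the table: 2,700/58 = 46.6 and 1,500/29 = 51.7 per village; total 5,700.
- By Appendix 1: 55 × 116 = 6,380, itself below the 6,500 stated.

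**Step 4: enrolment.** Table 7 gives no intra-cluster correlation. I took 35.1% as the control rate (Table 6) and 40.1% as the treated rate, with V = 2τ + 0.401 × 0.599/n₁ + 0.351 × 0.649/n₀. I then solved for the τ that gives the stated 80% at 55/55. The result is τ = 0.0047, a correlation of about 0.02.

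| Children per village (intervention/control) | V | Power at 5 points | MDE (points) |
|---|---|---|---|
| 55/55 | 0.0179 | 80% (by construction) | 5.0 |
| 51.7/46.6 (Table 3) | 0.0189 | 78% | 5.1 |
| 45/37.5 (note) | 0.0208 | 74% | 5.4 |
| 30/30 (15 non-farmer households × 2) | 0.0249 | 66% | 5.9 |

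**Step 5: what is not touched.** Test-score power at 0.2 SD falls by 0–2 points (for example 77% to 75% with s² = 0, if half the note's children are tested). HGSF+ versus regular feeding uses no control villages and has up to 10 farmers per village in both arms, so the control shortfall does not reach it.

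**The case against.** **The loss is small.** On the published inputs alone, 10/5 farmers gives 34% and 87%, within about a point of the printed 35% and 88%. The larger losses need an effect-size variance that the protocol never states. This stands, and it limits the point to a modest overstatement. Nor is all of the shortfall at 25% due to the control farmers: even 10/10 gives only 75–80% there, because the conclusions round 26% down to 25%.

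**The note may be the slip, not the table.** Appendix 1 cites a mean of 2.58 children aged 5 to 15 in rural Mali. With 2.58 per non-farmer household, control has 870 × 2.58 + 435 = 2,680 children and each feeding arm 435 × 2.58 + 435 = 1,557, close to Table 3's 2,700 and 1,500. A reader might infer that 4,785 is the true total and 74% the true enrolment power. The documents do not settle that.

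**Composition of the child sample.** Farmer households are 10 of 25 (40%) in intervention villages and 5 of 20 (25%) in control, and chiefs and committee members name them. A reader might infer that the child effects are therefore biased. The documents do not support that as stated. They nowhere say that the two household types are pooled for child outcomes, and the 15 non-farmer households per village match across arms. The planned difference-in-difference estimator also removes level gaps between household types. Only differing trends would matter, and the protocol gives no figure for those.

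**The protocol already warns about income power.** It does so in Other general equilibrium effects and in the appendix conclusions, where the stated insufficiency concerns the HGSF+ contrast. Neither warning corrects the school-feeding-versus-control inputs.

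**Conclusion.** The point holds, limited to school feeding versus control. The appendix inputs contradict the sampling plan, and 10 farmers is a ceiling in one arm and twice the ceiling in the other.

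- **Income:** the MDE is about 27% on published inputs, or 28–29% with an added effect-size variance of 0.05–0.06, against the stated 26% and 25%. Power at 25% is about 69–73%, part of that shortfall being due to rounding.
- **Enrolment:** power at 5 points is about 78% on Table 3's counts or 74% on its note, both conditional on the back-solved correlation of about 0.02.
- **Child totals:** three figures conflict, and only the sponsor can say which is right.

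The results assume a two-sided test and full recruitment to the farmer ceilings. No design change follows from them. Bias from farmer composition is a conditional matter, not a demonstrated error.

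**What to change.** 1. Rerun the school-feeding-versus-control power with 10 versus 5 farmers and the reconciled children per arm. State the enrolment intra-cluster correlation and any effect-size variance used, and restate the conclusions without rounding the MDE down.
2. Remove the word conservative from the Income section.
3. Correct Table 3's child column or its note, and the Appendix 1 text on 25 households in every village and more than 6,500 children.
4. State which households supply the child outcomes. If farmer and non-farmer households are pooled, include household type by survey round, or weight to equal farmer shares. If only the matched 15 + 15 non-farmer households are used, base the power on about 30 children per village (15 × 2), which gives roughly 66% for enrolment at 5 points under the same back-solved correlation.

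The cost is text and table corrections, one rerun of the power calculation and, if the samples are pooled, one stratum term or set of weights. The stated power will be slightly lower.
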